## Abstract

**Background:**

The follow-up of pediatric patients ensures regular ocular morbidity monitoring and better treatment outcome. Hiralal Santudevi Pradhan Institute of Ophthalmic Science (Bharatpur Eye Hospital [BEH]) noticed that the follow-up rate was only 22% among its pediatric patients. Several factors like lack of awareness and forgetfulness among patients may contribute to a lower number of follow-up visits. Therefore, BEH decided to find if counseling and reminders through SMS text messaging and phone calls would improve the follow-up rates.

**Objective:**

This study aims to evaluate the impact of interventions like counseling and reminder SMS text messaging and phone calls in improving the follow-up rate of pediatric patients.

**Methods:**

This is a public health intervention study being conducted using quantitative analysis. All children (0-16 years) with ocular conditions requiring at least 3 follow-up visits in the study period will be included. In all, 264 participants will be allocated to 3 groups: routine standard care, counseling, and reminders with SMS text messaging and phone calls. In counseling, patients will take part in 20-minute counseling sessions with trained counselors at each visit, and information leaflets will be provided to them. In the reminder SMS text messaging and phone call group, patients will receive an SMS text message 3 days prior and a phone call 1 day prior to their scheduled visits. Patients attending within 2 days of the scheduled date will be considered compliant to follow-up. The proportion of patients completing all the follow-up visits in each group will be assessed. Informed consent will be taken from parents and children. Univariate and multivariate analyses will be conducted.

**Results:**

The ethical approval for this study has been obtained from the Ethical Review Board (ERB) of Nepal Health Research Council (ERB protocol registration #761/2020 P). The data collection was initiated on January, 24, 2021, but due to the COVID-19 pandemic, as of September 2021, we have only been able to enroll 154 of the planned 264 participants (58.3% of the sample size).

**Conclusions:**

This study will reliably document not only the factors associated with follow-up rate through an intervention package (counseling and reminders through SMS text messaging and phone calls) but also the cost effectiveness of the intervention package, which can be applied in all the departments of the hospital.

**Trial Registration:**

ClinicalTrials.gov NCT04837534; https://clinicaltrials.gov/ct2/show/NCT04837534

**International Registered Report Identifier (IRRID):**

DERR1-10.2196/31578

## Introduction

Childhood visual impairment and blindness remains an important public health issue. It is estimated that around 14 million children in the world are blind [1]. The Nepal Pediatric Ocular Disease study found that the prevalence of blindness and visual impairment in the community was 0.068% (95% CI 0.02-0.12) and 0.097% (95% CI 0.04-0.15), respectively [2]. Increasing the global knowledge base for planning for childhood eye care services is a top priority in order for children with visual impairment to realize their full visual potential [3]. Follow-up of pediatric patients is important for their regular ocular morbidity monitoring, especially for amblyopia management [4]. Bharatpur Eye Hospital (BEH) observed that there was poor adherence to follow-up visits. An exploratory observation of data of the first week (January 1, 2010, to January 7, 2019) revealed that the follow-up compliance was very low among children aged 0 to 16 years in the pediatric department. Among the children advised for follow-up, only 22% were found to have come for at least 1 follow-up visit. A problem analysis showed that a lack of awareness in children and their parents regarding the importance of follow-up and patients forgetting dates of the follow-up visit (usually when there is long gap for follow-up) may be the major contributing factors for poor adherence to follow-up.

A study from India revealed that distance and cost were major barriers, as was the inability of the eye care center to communicate the importance of follow-up [5]. Another study done in Nepal found poor follow-up rates for patients following cataract surgery, which, however, improved after implementation of a high-quality pediatric counseling service, follow-up program, tracking system, and cell phone reminders [6]. Many studies have compared different methods of reminder options like telephone calls, email, and SMS text messaging in order to improve the compliance to follow-up [7-10]. Hence, a public health intervention study has been planned to estimate the effect of intervention package (counseling and reminder SMS texts and phone calls) for improving the follow-up rates in pediatric patients.

The primary objectives are to determine if parental counseling has an impact on adherence to follow-up and to determine if reminders through phone calls and SMS texts increase the follow-up rate in pediatric patients. The secondary objective is to assess the cost-effectiveness of counseling and reminder SMS texts and phone calls. We hypothesize that counseling will increase the follow-up rate from 22% to 50% and reminders through phone calls and SMS texts will increase the follow-up rate from 22% to 25% at the site of the study (mentioned in the next section).

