### Sample Size

Bonferroni correction (level of significance *P*=.05; k=3 comparisons) was adopted for sample size calculation with consideration to the proportion of attendance in counseling (p1) and reminder SMS texts and phone calls (p2) as 50% (0.5) and 25% (0.25), respectively. An estimated sample size of 264 pediatric patients will be targeted with an adjusted significance level of .02, 80% power, and 10% loss to follow-up.

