### Outcomes

The primary outcome is the proportion of children completing all 3 follow-up visits in the routine standard care group, counseling group, and reminders through SMS texts and phone call group.

The secondary outcomes include the effect of parental or guardian education status in compliance to follow-up, the visual status of the children in subsequent follow-up visits, the effect of traveling distance and cost in compliance to follow-up, and the cost-effectiveness of the intervention.

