### Compliance to Follow-up

The participants’ first visit to the hospital and the scheduled 3 follow-up visits need to be completed for them to be considered compliant to the follow-up. Only those participants who complete the first follow-up will be considered for second follow-up, and only those coming for second follow-up will be considered for third follow-up [6]. The patient will be considered compliant to follow-up if he or she comes within the window period of 2 days. The rescheduling of the next follow-up date will be calculated from the attended date as per the follow-up schedule for each ocular condition.

The purpose of observing compliance to follow-up is to determine the impact of counseling and reminders through SMS texts and phones call for the increment of the proportion of children completing their 3 follow-up visits based on the developed proforma and to find out the significant proportion in the follow-up rate between the 3 different groups.

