## Results

Descriptive statistics will be presented, and demographic variables will be summarized by computing means with SD for continuous variables and proportions for categorical variables. Associations between sociodemographic variables and compliance rates will be presented. The associations will be computed using categorical variables. Two dry runs were conducted to assess the logistics and flow of participants. The first dry run was conducted by taking only 10 patients who were not the actual study participants, but the second dry run was conducted with the actual participants as per the inclusion and exclusion criteria. A total of 38 study participants were enrolled for a duration of 1 month for the second dry run. Of these participants 13, 13, and 12 were divided into the standard care group, counseling group, and reminder with SMS texts and phone call groups, respectively. The mean age of the children was 3.71 (SD 0.61) years, with a range of 0.07 to 14 years. There were more male children 24 (63.16%) as compared to female children 14 (36.84%). Most of the children were of Aryan descent (63%), and more than 80% of the children were accompanied by their mother. Only 7 out of the 38 patients attended the follow-up visit. All those who attended have attended only the first follow-up visit. Three participants were from reminder group, two were from the counseling group, and two were from the standard care group. Out of the 38 children, 14 (36.8%) were diagnosed with congenital naso-lacrimal duct obstruction and 7 with amblyopia, with the others having conjunctivitis, eye injury, corneal ulcer, or squint.

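### The planning rates appear to count children who return at least once, but the primary outcome is all 3 visits within 2 days, so the stated 80% power is not substantiated for it

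*Protocol article*

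**What the plan says.** Three parts of the protocol article bear on this.

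- **Baseline and hypotheses (Introduction).** Among children advised to return, "only 22% were found to have come for at least 1 follow-up visit". No window around the scheduled date is mentioned. The hypotheses start from that figure: "We hypothesize that counseling will increase the follow-up rate from 22% to 50" percent, and "reminders through phone calls and SMS texts will increase the follow-up rate from 22% to 25" percent.
- **Sample Size.** The inputs are the "proportion of attendance in counseling (p1) and reminder SMS texts and phone calls (p2) as 50% (0.5) and 25% (0.25), respectively". With a Bonferroni correction for 3 comparisons (adjusted level printed as .02), 80% power and 10% loss, the target is 264 children.
- **Outcomes and Compliance to Follow-up.** "The primary outcome is the proportion of children completing all 3 follow-up visits in the routine standard care group", and likewise in the other two groups. Visits count in sequence, so a child who misses one is not considered for the next. A window also applies: "The patient will be considered compliant to follow-up if he or she comes within the window period of 2 days". Under Record Maintenance, later attendance is recorded but does not count as compliance.

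The Results section reports a second dry run of 38 children, of whom 7 returned: "All those who attended have attended only the first follow-up visit".

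**The concern.** The baseline and the primary outcome are different events. A child who returns once, on any date, counts toward the 22%. A child counts toward the primary outcome only after three successive visits, each on time. The second event is contained in the first, so within any group its rate is equal or lower.

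Both hypotheses use one term, follow-up rate, and one starting value, so the 50% and 25% appear to be on the at-least-one-visit scale. If so, the calculation powers a comparison that the trial will not make as its primary one. Lower completion rates can bring the groups closer in absolute terms and reduce power.

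The Discussion says that an effective intervention will become hospital policy. Readers of a non-significant result need to know what difference the trial could have detected on the outcome it tested.

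**Working it through.** **1. Reproduce the stated size.** Inputs from Sample Size: p1 = 0.50, p2 = 0.25, alpha = 0.05/3 = 0.0167, power 80%, loss 10%. Two-sided testing is assumed, since sidedness is not stated.

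n = [z(alpha/2)·√(2p̄(1−p̄)) + z(beta)·√(p1(1−p1) + p2(1−p2))]² / (p1−p2)², with p̄ = 0.375, z(alpha/2) = 2.394 and z(beta) = 0.842.

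This gives 77.1, so 78 per group. 78/0.9 = 86.7, so 87, and 3 × 87 = 261, close to 264. Taking .02 literally gives 74, then 83, then 249. The arithmetic is sound for 50% versus 25%. The question is what those rates measure.

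**2. Numbers per group.** 264/3 = 88, and 88 × 0.9 = 79.2 evaluable. The power figures below use 80 per group; 79 changes them by no more than about one percentage point.

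**3. Move to the primary-outcome scale.** The article gives no all-3 rate, so a model must be assumed. Let the planning rate p be the chance of an in-window first follow-up visit, and r the chance of making each later visit in its window, given the one before. Then

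all-3 rate = p × r².

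Example: counseling at r = 0.8 is 0.50 × 0.64 = 32%; control is 0.22 × 0.64 = 14.1%; reminders 0.25 × 0.64 = 16%.

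Power is the exact binomial power of the two-sided chi-square test without continuity correction, alpha 0.05/3.

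*Same r in every group:*

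| r | Counseling / control / reminder, all 3 | Power vs control | Power vs reminder |
|---|---|---|---|
| 1.0 | 50% / 22% / 25% | 91% | 82% |
| 0.9 | 40.5% / 17.8% / 20.3% | 79% | 66% |
| 0.8 | 32% / 14.1% / 16% | 62% | 49% |
| 0.7 | 24.5% / 10.8% / 12.3% | 46% | 35% |
| 0.5 | 12.5% / 5.5% / 6.3% | 20% | 15% |

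*Counseling also raises later return (r in counseling, then r in the comparator):*

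| r | Counseling / control / reminder, all 3 | Power vs control | Power vs reminder |
|---|---|---|---|
| 0.8, 0.7 | 32% / 10.8% / 12.3% | 83% | 75% |
| 0.8, 0.6 | 32% / 7.9% / 9% | 94–95% | 91% |
| 0.7, 0.6 | 24.5% / 7.9% / 9% | 70% | 61% |
| 0.6, 0.5 | 18% / 5.5% / 6.3% | 54% | 46% |

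**4. What a 50% all-3 rate would require.** With equal attendance at each visit, 0.5^(1/3) = 0.794, so about 79% in-window attendance at every visit.

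**5. The dry run.** 7/38 = 18.4% returned at all, and none went beyond the first follow-up. Enrollment lasted one month and the observation time is not stated. In Results, 14 children had naso-lacrimal duct obstruction and 7 had amblyopia; Table 1 schedules both every 4 weeks. So 21 of 38 (55%) needed about 12 weeks to reach a third visit.

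**The case against.** **The interventions are repeated.** Counseling is given at every follow-up visit, and reminders precede every scheduled visit. Equal later return in all groups, which produces the low power figures, therefore sits uneasily with the design. This stands. If counseling holds children better at visits 2 and 3, power can match or exceed 80%. But the unequal values of r are assumptions too. Reminders may also improve later return, and if they match counseling at r = 0.8, that comparison is back at 49%. A reader might infer that the trial is shown to be underpowered for counseling, or that a null result would merely reflect a wrong planning rate. The documents support neither.

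**The 22% is not a sample-size input, and 50% and 25% are never expressly called at-least-one-visit rates.** Both statements are correct, which is why the point says that the rates appear to be on that scale. If they were meant as all-3 rates, the hypotheses would set an all-3 target against an at-least-one-visit baseline, and that would need correcting as well.

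**The dry run confirms low completion.** A reader might infer this from none of 38 going beyond the first visit. With unstated observation time and mostly 4-weekly schedules among those enrolled, third visits may simply not have fallen due. It is weak support, and the point does not depend on it.

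**An article condenses the full protocol.** True, but the baseline definition, the hypotheses and the primary outcome are all printed here, and they do not match.

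**Conclusion.** The concern holds as a mismatch of definitions. The 264 is correctly computed for 50% versus 25%, but those targets are tied to a baseline for returning at least once, and nothing carries them over to completing 3 in-window visits. The stated 80% power is therefore not substantiated for the primary outcome.

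The mismatch rests on the text alone. The size of the effect on power does not: in the scenarios shown it runs from 20% to about 95% for counseling versus control and from 15% to 91% for counseling versus reminders, depending on an assumed later-visit return that the documents do not give. A loss is plausible. Its amount is unknown.

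**What to change.** 1. In the hypotheses at the end of the Introduction, label the 22% as the at-least-one-visit rate and say which outcome the 25% and 50% refer to.
2. In Sample Size, state the assumed rate of completing all 3 visits within 2 days for each group, with its basis. Use hospital records if they hold scheduled dates; otherwise give a range and say that it is assumed.
3. Replace the single 80% with power over that range at about 79 evaluable children per group (88 less 10%), covering both equal and unequal later-visit return.
4. Optionally, add a supportive secondary comparison of the number of in-window visits completed (0 to 3) over all allocated children. It should not be presented as keeping a fixed power, because that would hold only if the whole effect fell on the first visit. It does not repair the power of the primary test.

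The cost is a records query where feasible, a rewritten sample-size paragraph and, if chosen, one more analysis of data already collected. The primary outcome is unchanged. The downside is that the stated power may become less favorable.

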## Methods

### Study Design and Setting

This public health intervention study will be conducted at Hiralal Santudevi Pradhan Institute of Ophthalmic Sciences which includes 13 satellite clinics and 1 base hospital (Bharatpur Eye Hospital [BEH]). The study participants will be enrolled only from the pediatric department of BEH, a centrally located tertiary eye hospital in the Chitwan district of Nepal. All pediatric patients 0 to 16 years of age meeting the inclusion criteria will form the study population. In the pediatric department of BEH, children aged 0 to 16 years are being examined as per the hospital policy.

The inclusion criteria are all pediatric patients 0 to 16 years of age advised for at least 3 follow-up visits within a 6-month period at BEH, parents or guardians of children who own a mobile phone or have daily access to a phone and are able to use the SMS text feature on these phones, and parents willing to enroll their children in the study.

The exclusion criteria are children who require fewer than 3 follow-up visits, children with ocular conditions requiring daily follow-up visits (because it is not feasible to send the reminder phone call and SMS text for daily follow-up), children who have already been treated and are under regular follow-up, children with ocular conditions requiring follow-up beyond 6 months, parents or guardians of the children who are not willing to participate in the study, and those who have been called but do not answer after 3 attempts

### Sample Size

Bonferroni correction (level of significance *P*=.05; k=3 comparisons) was adopted for sample size calculation with consideration to the proportion of attendance in counseling (p1) and reminder SMS texts and phone calls (p2) as 50% (0.5) and 25% (0.25), respectively. An estimated sample size of 264 pediatric patients will be targeted with an adjusted significance level of .02, 80% power, and 10% loss to follow-up.

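### Bonferroni over three comparisons, the only multiplicity rule stated, is valid but needlessly inefficient for three groups; a step-down rule would add about 3 to 7 points of power if that level governs the final tests

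*Protocol article*

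**What the plan says.** The Sample Size section adopts a Bonferroni correction, with overall level .05 and "k=3 comparisons) was adopted for sample size calculation". It takes the rates for counseling and reminders "as 50% (0.5) and 25% (0.25), respectively", and sizes the trial "with an adjusted significance level of .02, 80% power, and 10% loss to follow-up". The result is given as "An estimated sample size of 264 pediatric patients will be targeted".

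The Introduction supplies the third rate: routine care is put at 22%, with counseling raising it to 50% and reminders to 25%. The primary objectives there concern the effect of counseling on adherence and, second, to "determine if reminders through phone calls and SMS texts increase the follow-up rate in pediatric patients". The Compliance to Follow-up section describes the purpose as "to find out the significant proportion in the follow-up rate between the 3 different groups".

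The Univariate Analysis and Multivariate Analysis sections plan logistic regression with odds ratios and ordinary 95% confidence intervals. Neither names a multiplicity rule for the final tests.

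**The concern.** The three pairwise nulls among three groups are linked. If routine care and counseling differ, reminders cannot equal both, so at most one of the remaining two nulls can be true. Bonferroni ignores this link and holds every comparison to .05/3 = .0167, even after one difference has been shown.

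A rule that uses the link keeps every Bonferroni rejection and can only add to them, at the same nominal family-wise error. If .0167 is carried into the analysis, the trial loses power on its two primary objectives and on counseling vs reminders, the pair whose rates enter the sample size calculation.

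**Working it through.** **Inputs.** Rates of 22% (routine care), 50% (counseling) and 25% (reminders) from the Introduction and Sample Size sections; overall level .05, three comparisons, 80% power, 10% loss and N = 264 from Sample Size. Assumptions: two-sided tests (sidedness is not stated), pooled two-proportion z tests, and the three comparisons being the three group pairs.

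**1. Reproduce the sample size.** n = [z(α/2)·√(2p̄(1−p̄)) + z(β)·√(p1(1−p1)+p2(1−p2))]² / (p1−p2)², with p1 = .50, p2 = .25, p̄ = .375.
- α = .05/3: z = 2.394, so (2.394 × .6847 + .842 × .6614)² / .0625 = 77.1, i.e. 78 per group. 78/.9 = 86.7, i.e. 87; 3 × 87 = 261.
- α = .02 as printed: z = 2.326 gives 73.9, i.e. 74. 74/.9 = 82.2, i.e. 83; 3 × 83 = 249.

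The stated 264 is close to the .05/3 result, so .02 looks like a rounding of .0167.

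**2. Evaluable size.** 264/3 = 88 per group; 88 × .9 = 79.2, i.e. 79.

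**3. Analytic check at 79 per group, 50% vs 25%, α = .05/3.** Φ[(.25 × √79 − 2.394 × .6847)/.6614] = Φ(.88) = 81%, in line with the simulated 82% below.

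**4. Simulated power** (at least 400,000 trials; 79 per group; 22%/50%/25%). Step-down means: smallest P at .05/3; if it passes, the other two at .05.

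| Comparison | Bonferroni .05/3 | Printed .02 | Step-down | Unadjusted .05 |
|---|---|---|---|---|
| Counseling vs routine care | 91.1% | 92.1% | 94.0% | 96.4% |
| Counseling vs reminders | 81.8% | 83.1% | 89.2% | 91.0% |
| Reminders vs routine care | 2.8% | 3.1% | 7.4% | 7.4% |

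The gain over .05/3 is about 3, 7 and 5 points; over .02 it is about 2, 6 and 4. Power to win both counseling contrasts rises from 77% to 88%. Ordinary Holm (.0167, .025, .05) gains only about 1, 4 and 3 points, so the rule has to be named exactly.

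**5. Family-wise error at 79 per group.** With all three groups at 22%: Bonferroni 4.4%, step-down 4.4%, unadjusted about 12%. With only counseling effective (22%/50%/22%): Bonferroni 1.7%, step-down 5.1%. The highest step-down value found was 5.5% (22%/50%/50%, 88 per group), which reflects the discreteness of the z test; the nominal level is 5%.

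**6. Sensitivity (79 per group unless stated).**
- Counseling at 40% (assumption): counseling vs reminders 36% to 46%, counseling vs routine care 53% to 58%.
- Reminders at 35% (assumption): reminders vs routine care 29% to 44%, while counseling vs routine care gains only about 1 point.
- 154 enrolled as of September 2021, about 51 per group with no loss: counseling vs reminders 60% to 71%.

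**The case against.** The strongest reply is that the article ties Bonferroni to sizing only. A reader might infer that each final comparison must reach .05/3, but no section says so, and the analysis sections quote plain 95% intervals. A conservative sizing rule does not prevent a sharper testing rule later, and a statistical analysis plan that is not shown may contain one. This stands, and it makes the power gain conditional. If the final tests were run at an unadjusted .05, the step-down rule would lower power slightly (96.4% to 94.0% and 91.0% to 89.2% on the counseling contrasts, no change on reminders vs routine care). Its benefit would then be error control. Stating it therefore helps on either reading, but for different reasons.

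A reader might also infer that Bonferroni is a mistake here. It is not: at .05/3 it controls the error, and the sized pair has 82% power against the planned 80%.

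Nor do the plan's own figures support a gain of 15 points. That size of gain requires a reminder rate of about 35%, where the article assumes 25%.

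Finally, a reader might hope that the change rescues the reminder objective. At 22% vs 25% its power stays below 8% under every rule examined.

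**Conclusion.** The point holds as an improvement in efficiency, not as the correction of an error. If .05/3 governs the final tests, the three-group step-down rule gains about 3, 7 and 5 points of power at the plan's rates and 79 evaluable per group, at the same nominal 5% family-wise error and with no added patients. Measured from the printed .02, the gains are about 2, 6 and 4 points, and the comparison of error rates is less clean because 3 × .02 = .06 already exceeds .05. If the final tests would be unadjusted, the rule instead brings family-wise error under the global null from about 12% to 4.4%, for about 2 points of power on the counseling contrasts.

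That the step-down rule rejects whenever Bonferroni at .05/3 does, and holds the nominal level, is a matter of logic and needs no assumed rates. The sizes rest on the plan's three rates, 10% loss, two-sided pooled z tests and a family of three pairwise comparisons.

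**What to change.** Keep 264. For the primary analysis, state: the three pairwise comparisons are ordered by P value; the smallest is tested at .05/3; if it is significant, the other two are each tested at .05; if it is not, testing stops. Fix this before any outcome is compared by group.

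The cost is two or three sentences, with no extra patients, visits or data. There is one small downside: simultaneous confidence intervals do not match the step-down decisions one-to-one. Little is lost, because the plan reports ordinary 95% intervals; if simultaneous intervals are wanted, 98.33% intervals (1 − .05/3) can be shown alongside.

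### The single 80% power figure belongs to counseling versus reminder; on the protocol's own rates, the primary reminder objective (22% to 25%) has about 3% power

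*Protocol article*

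**What the plan says.** The Introduction of the protocol article sets two primary objectives: whether counseling affects adherence, and "to determine if reminders through phone calls and SMS texts increase the follow-up rate in pediatric patients". Each carries a numerical hypothesis against the same 22% baseline. For counseling: "We hypothesize that counseling will increase the follow-up rate from 22% to 50" (percent). For reminders: "reminders through phone calls and SMS texts will increase the follow-up rate from 22% to 25" (percent).

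The Sample Size section applies a Bonferroni correction for "k=3 comparisons" and takes only two rates as inputs: "the proportion of attendance in counseling (p1) and reminder SMS texts and phone calls (p2) as 50% (0.5) and 25% (0.25), respectively". It concludes: "An estimated sample size of 264 pediatric patients will be targeted with an adjusted significance level of .02, 80% power", with 10% loss to follow-up. It gives no rate for routine care and no power for any individual comparison.

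Three other places bear on the point. The Outcomes section makes completion of all three follow-up visits the primary outcome, reported for all three groups. The Introduction defines the 22% as attendance at one or more follow-up visits. The Discussion says that interventions shown to be effective will be extended to other departments and become hospital policy.

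**The concern.** A reader who meets one unqualified power figure next to two primary objectives will take it to cover both. It does not. The inputs are the two intervention rates, which differ by 25 percentage points, whereas the reminder hypothesis is a difference of 3 points from routine care. A trial sized for the first has almost no chance of detecting the second.

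What is at stake is the adoption decision. If reminders raise completion exactly as hypothesized, the trial will very probably not declare them effective, so under the policy in the Discussion they would probably not be adopted. Nothing in the stated sample size warns the reader of this.

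**Working it through.** **Inputs.** Rates of 50% (counseling), 25% (reminder) and 22% (routine care) come from the Introduction and Sample Size sections. The adjusted alpha is .05/3 = .0167, printed as .02. Power is 80%, loss is 10% and the total is 264. Equal allocation (the fixed rotation in Study Procedure) gives 264/3 = 88 per arm, or 88 × 0.9 ≈ 79 after loss. Sidedness is not stated, so two-sided is assumed.

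**Formula.** Two proportions, pooled variance under the null, no continuity correction, with p̄ the mean of the two rates:

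n per arm = [z(1−α/2)·√(2p̄(1−p̄)) + z(0.80)·√(p1(1−p1) + p2(1−p2))]² / (p1−p2)²

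where z(1−α/2) = 2.394 at α = .0167 and z(0.80) = 0.842.

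**Step 1: reproduce 264.** For 50% vs 25%, p̄ = 0.375, so n = (2.394 × 0.6847 + 0.842 × 0.6614)² / 0.25² = (1.639 + 0.557)² / 0.0625 = 77.1, rounded up to 78. With 10% loss, 78/0.9 = 86.7, so 87 per arm and 261 in total, within 1.1% of the stated 264. The other contrasts do not give 264:

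- 50% vs 22% needs 60.1, so 61 per arm, or 204 in total with loss (228 with continuity correction).
- 25% vs 22% needs about 4,182 evaluable per arm, or about 4,647 enrolled per arm with loss.

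The stated size therefore matches counseling versus reminder.

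**Step 2: power of the same 264 children for each contrast.** Exact binomial enumeration of the two-sided pooled z-test at α = .0167:

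| Contrast | Rates | 79 per arm | 88 per arm |
|---|---|---|---|
| Counseling vs routine care | 50% vs 22% | 91% | 94% |
| Counseling vs reminder | 50% vs 25% | 82% | 86% |
| Reminder vs routine care | 25% vs 22% | 2.8% | 3.0% |

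The normal approximation for the last row shows why. At 79 per arm, the standard error of the difference is √[(0.25 × 0.75 + 0.22 × 0.78)/79] = 0.0674. The critical difference is 2.394 × 0.0675 = 0.161, against a hypothesized 0.03. Power is then Φ((0.03 − 0.161)/0.0674) = Φ(−1.95) = 2.6%, plus 0.2% in the wrong tail.

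**Step 3: sensitivity of the reminder figure.**

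- α = .02 as printed: 3.1% to 3.4% (exact).
- One-sided at .0167 to .02: 4.6% to 5.6%.
- Unadjusted two-sided α = .05: 7.4% to 7.7% (exact).

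No variant comes near 80%.

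**Step 4: what the trial can detect.** The reminder rate at which power against 22% reaches 80% (α = .0167) is 46.2% with 79 per arm and 44.9% with 88. That is a difference of about 23 to 24 points, roughly eight times the hypothesized 3.

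**Step 5: precision.** At 25% vs 22% with 79 per arm, the 95% interval for the difference has a half-width of 1.96 × 0.0674 = 0.132, about 13 points.

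**The case against.** The strongest reply is that counseling versus reminder is a legitimate planned comparison. Three groups and three comparisons imply all pairs, the Compliance to Follow-up section looks for differences among the three groups, and the Discussion asks which strategy works better. Two of the three contrasts, including the counseling objective, have at least 80% power. All of this stands. The calculation of 264 is not wrong, and the defect is confined to the reminder objective. It does not remove the problem, because the Introduction states the reminder hypothesis numerically against 22%.

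A second reply is that the 22% is attendance at one or more visits, while the primary outcome is completion of all three, each within a 2-day window. In the second dry run, 7 of 38 children attended, and only for the first follow-up. This also stands. Every power figure here is conditional on the protocol's stated rates, and any replacement text must say so. It gives no support to the unqualified 80%.

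Three stronger readings are tempting, and the documents do not support them:

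- **That a null result would remove reminders.** Routine care includes no reminders, and the Discussion speaks only of adopting what is found effective. The realistic consequence is non-adoption.
- **That the protocol will read non-significance as no effect.** It does not say so. It leaves the reading open.
- **That the reminder comparison yields no information.** An interval of about ±13 points around a 3-point difference would run from about −10 to +16. It would exclude an effect as large as the 28 points hypothesized for counseling, but could not separate a modest benefit from none. The analysis sections already plan odds ratios with 95% intervals, so reporting an interval is partly provided for.

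**Conclusion.** The point holds for one of the two primary objectives. The stated 80% refers to counseling versus reminder. For reminder versus routine care at the protocol's own 22% and 25%, power is about 3%, barely above the adjusted alpha. The counseling objective is adequately powered on the stated rates.

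This rests on the rates as printed, equal arms of 79 to 88, and a two-sided test. Rounding alpha to .02 or testing one-sided changes the reminder figure by at most a few points and leaves the conclusion unchanged. It should be corrected, because the power statement as written is wrong for a hypothesis that the same article states numerically.

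**What to change.** Rewrite the Sample Size section to do the following:

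1. Say that the 80% refers to counseling (50%) versus reminder (25%).
2. Give power for each contrast at α = .0167 with 79 to 88 per arm: about 91–94% for counseling versus routine care, 82–86% for counseling versus reminder, and about 3% for reminder versus routine care.
3. State that these figures are conditional on the assumed rates, and that the 22% is attendance at one or more visits while the primary outcome is all three.
4. State that the smallest reminder rate detectable against 22% with 80% power is about 45–46%, and that the 22% to 25% hypothesis lies far below it.

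In the analysis and reporting text, present reminder versus routine care as an estimate with its confidence interval, and state that a non-significant result will not be interpreted as no effect.

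The hypothesis need not be withdrawn and no extra patients are needed. With 154 of 264 enrolled as of September 2021, the article describes a trial still recruiting, so the clarification could be made before analysis. The only cost is a less favorable stated power for one objective.
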